**FIGURE 1 bco270057-fig-0001:**
[figure not shown]
Flow diagram outlining the treatment cohort.

#### Institutional standard of care treatments

5.1.1

*rRPLND*: Participants undergoing rRPLND will have robot‐assisted laparoscopic surgery to remove ipsilateral retroperitoneal lymph nodes(s) as per local Trust procedures. For participants undergoing rRPLND, adjuvant treatment decisions are based on post‐operative histology and is left to the shared decision‐making between treating clinician and participants as per local SOC. The adjuvant treatments typically used following rRPLND are summarised in Table 1. Data will be collected on the type of adjuvant treatment delivered.

**TABLE 1 bco270057-tbl-0001:** Typically‐used adjuvant treatments following rRPLND.

Post‐operative nodal histology	Adjuvant treatment
pN0 or pN1 teratoma only	No adjuvant treatment
pN1 mixed/NSGCT	1x Bleomycin, etoposide and platinum (BEP), OR 2x Etoposide and cisplatin (EP)
pN1 seminoma	1x Carboplatin AUC7 or 10
pN1 positive surgical margins	2x BEP, OR 2x EP (NSGST), OR 2x Carboplatin AUC10 (Seminoma)

*Carboplatin AUC10*: Carboplatin AUC10 is typically given intravenously once every 21 days for 3 cycles (as per local Trust procedures).

*BEP/EP*: BEP is given intravenously every 21 days over 3 cycles while EP is given intravenously every 21 days over 4 cycles (as per local Trust procedures).

*Radiotherapy:* Radiotherapy is delivered with 30Gy in 15 fractions to para‐aortic nodes and 5Gy in 3 fractions to ipsilateral iliac nodes. Alternatively, a single cycle of Carboplatin (AUC7) is followed by 30Gy in 15 fractions to para‐aortic nodes (as per local Trust procedures).

All agents listed above are non‐investigational medicinal products licensed in the UK for treatment of TGCT. Information regarding anti‐cancer treatments will be collected for all participants throughout the follow‐up period.

### Sample size

5.2

This is a 30‐participant feasibility study across 2 cohorts with an 18‐month recruitment period. Hence, sample size calculation is not appropriate, but the recruitment target is typical for feasibility studies.^13^

### Study timeline

5.3

The tables below describe the participant timeline through the trial. Participants will attend visits according to the schedule outlined in Table 2 for the rRPLND cohort and Table 3 for the Carboplatin AUC10 cohort. These visits will include screening, treatment and follow‐up assessments to monitor progress and outcomes.

**TABLE 2 bco270057-tbl-0002:** Schedule of assessments for rRPLND cohort.

	Screening	rRPLND	2 weeks	6 weeks	12 weeks	6 months	9 months	12 months	15 months	18 months	21 months	24 months	Disease recurrence
	<6 weeks pre‐surgery		± 2 weeks	± 2 weeks	± 2 weeks	± 2 weeks	± 2 weeks	± 4 weeks	± 4 weeks	± 4 weeks	± 4 weeks	± 4 weeks	+4 weeks
**Informed consent**	X												
**Demographic data & medical history**	X												
**Blood tests** ^**1**^	X		X	X^7^	X	X	X	X	X	X	X	X	X
**EDTA creatinine clearance**				X^2^									
**Fitness for surgery**	X												
**Imaging (RECIST v1.1)**	X				X			X				X	X
**Institutional SOC treatment**		Participants will receive either rRPLND or other institutional SOC treatment if not eligible/decline rPLND Treatment details will be collected on the Case Report Forms (CRF)		Participants to receive adjuvant chemotherapy if applicable									
**Surgical outcome & complications**			X	X	X	X							
**Adverse events**		AEs will be collected from the date of consent until 6 weeks post rRPLND or the end of treatment depending on the allocated treatment.^6^											
**Tumour sample**	X^3^	X											
**Research blood sample**	X		X		X^7^								X
**Patient reported outcomes** ^**4**^	X		X	X	X	X		X		X		X	X
**Disease, treatment, survival FU** ^**5**^						X	X	X	X	X	X	X	X

^1^
Serum tumour markers, urea and electrolytes, liver function tests and full blood count. Tests may be carried out up to ≤72 hours before the day of treatment.

^2^
To be carried out prior to adjuvant treatment only for participants who undergo chemotherapy.

^3^
Archival FFPE tumour sample from previous biopsy or orchidectomy.

^4^
Patient reported outcome information collected via questionnaires: EORTC QLQ‐TC26, EORTC QLQ‐C30, BMSFI and supplementary questions.

^5^
Disease, treatment and survival follow‐up information may be collected in clinic or via a telephone call with the participant.

^6^
For participants that are not eligible/decline rRPLND, AEs will be collected from the date of consent until 6 months post the end of treatment depending on the allocated treatment.

^7^
Only for participants that receive adjuvant chemotherapy.

**TABLE 3 bco270057-tbl-0003:** Schedule of assessments carboplatin AUC10 cohort.

	Screening	Chemotherapy (cycle 1–3)	2 weeks	6 weeks	12 weeks	6 months	9 months	12 months	15 months	18 months	21 months	24 months	Disease recurrence
	<2 weeks prechemotherapy		± 2 weeks	± 1 week	± 2 weeks	± 2 weeks	± 2 weeks	± 4 weeks	± 4 weeks	± 4 weeks	± 4 weeks	± 4 weeks	+4 weeks
**Informed consent**	X												
**Demographic data & medical history**	X												
**Blood tests** ^**1**^	X	X	X		X	X	X	X	X	X	X	X	X
**EDTA creatinine clearance**	X												
**Imaging** *(RECIST v1.1)*	X		X					X				X	X
**Institutional SOC Treatment**		Participants will receive either Carboplatin AUC10 or other institutional SOC treatment if not eligible/decline Carboplatin AUC10. Treatment details will be collected on the CRF.											
**Adverse events**	AEs will be collected from the date of consent until 6 months post the end of treatment depending on the allocated treatment.												
**Tumour sample**	X^2^												
**Research blood sample**	X		X										X
**Patient reported outcomes** ^**3**^	X		X	X	X	X		X		X		X	X
**Disease, treatment and survival FU** ^**4**^						X	X	X	X	X	X	X	X

^1^
Serum tumour markers, urea and electrolytes, liver function tests and full blood count. Tests may be carried out up to ≤72 hours before the day of treatment. Test might be carried pre‐treatment for every cycle.

^2^
Archival FFPE tumour sample from previous biopsy or orchidectomy.

^3^
Patient reported outcome information collected via questionnaires: EORTC QLQ‐TC26, EORTC QLQ‐C30, BMSFI and supplementary questions.

^4^
Disease, treatment and survival follow‐up information may be collected in clinic or via a telephone call with the participant.

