### Intervention

5.1

Participants will receive SOC treatments for good prognosis stage II seminoma and NSGCT or de‐escalated treatments (primary rRPLND with or without adjuvant treatment or Carboplatin AUC10) for stage II seminoma. Participants will be allocated to one of the following two cohorts based on whether the relevant de‐escalated treatment is adopted as an institutional SOC:rRPLND cohort: Participants with ipsilateral stage IIA or <3 cm IIB seminoma with negative/low for tumour markers will be offered rRPLND followed by adjuvant treatment or surveillance based on post‐operative histology as per institutional SOC.Carboplatin AUC10 cohort: Participants with stage II seminoma will be offered Carboplatin AUC10 by 3 cycles.

Participants deemed ineligible for Carboplatin AUC10 or rRPLND or those who decline this de‐escalation option will be offered either BEP or EP chemotherapy (seminoma and NSGCT) or radiotherapy with or without neoadjuvant Carboplatin AUC7 (seminoma) and will continue to be followed in the study. Chemotherapy treatment strategies and adjuvant treatments are left to the shared decision‐making between treating clinicians and participants and follow institutional SOC. The study flow diagram outlining the treatment cohorts is summarised in Figure 1.

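### Table 2 is a surgical schedule that also governs participants who have no operation, so identical standard chemotherapy has different renal, on-treatment blood and first-scan data by cohort

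*Protocol article*

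**What the plan says.** Section 5.3 (Study timeline) ties the schedule to the cohort: "Participants will attend visits according to the schedule outlined in Table 2 for the rRPLND cohort and Table 3 for the Carboplatin AUC10 cohort". Section 5.1 (Intervention) places a participant in a cohort according to whether the de-escalated "treatment is adopted as an institutional SOC". The cohort therefore reflects where a participant is treated, not which treatment is given.

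Both tables state that they include people who do not receive the de-escalated option:

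- Table 2: "Participants will receive either rRPLND or other institutional SOC treatment if not eligible/decline rPLND".
- Table 3: "Participants will receive either Carboplatin AUC10 or other institutional SOC treatment if not eligible/decline Carboplatin AUC10".

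Under Section 5.1 that other treatment is BEP or EP chemotherapy, or radiotherapy for seminoma.

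Three rows then differ:

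- **Renal clearance.** In Table 2 the row "EDTA creatinine clearance" has a single mark, at 6 weeks, with the footnote "To be carried out prior to adjuvant treatment only for participants who undergo chemotherapy". In Table 3 the mark is at screening and is not restricted by treatment.
- **Blood tests.** Table 2 has no mark in the treatment column, and its 6-week mark is limited by footnote 7: "Only for participants that receive adjuvant chemotherapy". Table 3 has a mark in the column for chemotherapy cycles 1–3, with the footnote "Test might be carried pre‐treatment for every cycle".
- **Imaging.** The first scan after treatment is at 12 weeks (±2) in Table 2 and at 2 weeks (±2) in Table 3.

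The adverse-event row is the one place where Table 2 provides for participants without surgery. Footnote 6 gives them collection until 6 months after the end of treatment, the same as Table 3.

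**The concern.** A participant given BEP at an rRPLND site and one given BEP at a carboplatin site receive the same treatment but follow different schedules. Table 2 keeps its surgical frame for the first of them: a screening window counted back from surgery, a fitness-for-surgery row, a surgical-outcome row, and renal clearance tied to adjuvant treatment that a participant without an operation cannot have.

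The people affected are not only those who decline. Sections 4.1.1 and 4.1.2 limit both de-escalated options to seminoma, so every NSGCT participant receives SOC treatment. rRPLND is limited further by stage, node size and location, and markers.

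Safety of all treatments is a secondary objective (Section 3.2), and the Background says the prospectively collected safety information is meant to inform a future trial. If baseline renal clearance, on-treatment laboratory results and first response are collected in one cohort and not, or at another time, in the other, the analysis cannot restore what was never recorded. The Discussion says all rRPLND operations take place at a single centre. The schedule difference is therefore likely to be confounded with centre.

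**Working it through.** No sample-size or power figure is involved. The check compares Tables 2 and 3 cell by cell for a participant given primary BEP or EP, leaving out cells that apply only to adjuvant chemotherapy.

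| Item | Table 2 | Table 3 | Same? |
|---|---|---|---|
| Screening window | <6 weeks before surgery | <2 weeks before chemotherapy | No |
| EDTA clearance | none | screening | No |
| Bloods in treatment column | none | cycles 1–3 | No |
| Bloods at 6 weeks | none (adjuvant only) | none | Yes |
| Bloods at screening, 2 and 12 weeks, 6–24 months, recurrence | yes | yes | Yes |
| First post-treatment scan | 12±2 weeks | 2±2 weeks | No |
| Scans at 12 and 24 months, recurrence | yes | yes | Yes |
| Questionnaire visits | same visits | same visits | Yes (6-week window ±2 against ±1 week) |
| Research blood | screening, 2 weeks, recurrence | same | Yes |
| Survival follow-up | 6–24 months, recurrence | same | Yes |
| Adverse-event window | consent to 6 months after treatment | same | Yes |

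**Scan windows, same starting point in both tables.** Table 2: 12−2 = 10 to 12+2 = 14 weeks. Table 3: 2−2 = 0 to 2+2 = 4 weeks. Nominal gap: 12−2 = 10 weeks. Smallest gap: 10−4 = 6 weeks. Largest: 14−0 = 14 weeks. The windows do not overlap.

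**Length of treatment (Section 5.1.1).** BEP: 3 × 21 days = 63 days = 9 weeks. EP: 4 × 21 days = 84 days = 12 weeks. If visits count from the end of treatment, Table 2 has no scheduled blood test in these 9 or 12 weeks.

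**Dependence on the starting point.** Section 2 has both cohorts followed for 2 years after treatment completion, which supports counting from the end of treatment. Table 2 does not give the starting point for participants without surgery. If their clock ran from the start of treatment while Table 3's ran from the end:

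- The Table 2 scan would fall 10−9 = 1 to 14−9 = 5 weeks after BEP, or 10−12 = −2 to 14−12 = 2 weeks around the end of EP. Both overlap Table 3's 0–4 weeks.
- The 2-week blood test would fall during treatment.
- The EDTA difference would remain.

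**Number affected.** Section 2.2 caps SOC recruitment at 15. The split between cohorts is not given, so the number under Table 2 lies anywhere from 0 to 15.

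**The case against.** The strongest reply is that these tables schedule study data and do not direct care. The study is observational, and BEP, EP and radiotherapy follow local Trust procedures (Section 5.1.1). A reader might infer from Table 2 that cisplatin-based chemotherapy starts there with no renal check. The documents do not support that. Table 2 schedules screening bloods that include urea and electrolytes, allowed up to 72 hours before treatment, and a missing mark does not mean that a test is not done locally. What is absent is the EDTA measurement as a study item.

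A reader might also infer that pooled SOC safety data are not comparable, or that rRPLND sites will record fewer adverse events. Neither is shown:

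- The adverse-event window is the same in both tables, and Section 5.7 defines an adverse event without reference to scheduled tests.
- The sentence in Section 5.4 that turns blood abnormalities into adverse events follows one about tumour markers at screening, so it is a weak basis for a claim about blood counts or renal function.
- A pooled SOC safety analysis is implied by the abstract's two arms but is not specified.
- Scan timing bears on response and on dating early progression, not on safety.

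The Table 3 comparison has limits of its own. Testing before each cycle is only permitted, and the chemotherapy column does not clearly cover radiotherapy or a fourth EP cycle.

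These replies narrow the point but do not remove it. The authors adapted the adverse-event row for participants without surgery and left the renal, blood and imaging rows unchanged, so nothing in the tables ensures equal capture. Where tests are done locally, Table 3 lists them for study collection and Table 2 does not.

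**Conclusion.** The point holds in a limited form. For the same primary SOC chemotherapy, Table 2 schedules no EDTA clearance against one in Table 3, and no on-treatment blood test against a marked column. Its first post-treatment scan is nominally 10 weeks later (range 6 to 14). Baseline renal clearance, on-treatment laboratory toxicity, and first response or the dating of early progression may therefore be captured differently by cohort.

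The blood-test and scan parts assume that visits count from the end of treatment in both tables. The EDTA part does not depend on this. For radiotherapy the EDTA and scan differences apply as written, but the on-treatment blood contrast is unclear.

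At most 15 participants are in scope, with an unknown share under Table 2; any single figure within 0 to 15 would be a guess. Clinically reported adverse events and 2-year PFS are little affected, and the primary recruitment endpoint is untouched. This is an internal inconsistency worth correcting, not grounds to discount the study's safety data.

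**What to change.** Reconcile Tables 2 and 3 so that participants given the same SOC treatment follow one data-collection schedule whatever their cohort. A footnote to Table 2 would do, or a single SOC schedule referenced by both tables. It should state the point from which visits are counted for participants without surgery, and say how radiotherapy and the fourth EP cycle fit the treatment column. Which tests and timings are clinically right is for the investigators; this review takes no position on that.

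Until then, report SOC laboratory toxicity and first response by cohort, and say that the schedules differed.

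The cost is a table revision and some extra eCRF entry of tests performed locally. Section 2.1 already foresees an amendment to add sites, which could carry the change.

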### Methods of data collection

5.4

*Demographic data*: Age, sex, date of birth and race/ethnicity will be collected with participants' consent, along with a comprehensive medical history including previous conditions, surgeries, cancer history and detailed testicular cancer diagnosis.

*Blood samples*: Serum tumour markers (AFP, BhCG, LDH) will be taken at screening and analysed locally. Results will be recorded in CRF, with clinically significant treatment‐related abnormalities noted as AEs. For participants undergoing rRPLND, surgical outcomes will be recorded, including complications, hospital stay and recovery time, up to six months post‐surgery.

*Imaging*: Centres that perform rRPLND typically undertake a baseline PET scan prior to surgery to determine eligibility. Positron Emission Tomography (PET) is typically not used in centres treating participants with Carboplatin AUC10. PET is not mandated for this trial; however, if a baseline PET is undertaken as part of institutional SOC, the results will be collected. All tumour assessments will be performed using Computed Tomography (CT) scans following the schedule of assessments. If contrast CT is contraindicated, Magnetic Resonance Imaging (MRI) scans and non‐contrast CT scans may be used. RECIST v1.1 criteria will be used to assess participants response.

*Health‐related quality of life*: Will be assessed using standardised validated questionnaires (EORTC QLQ‐TC26, EORTC QLQ‐C30, BMSFI and additional bespoke enquires on anejaculation), self‐administered using paper‐based format by participants. Site staff will assist if needed and document reasons for any uncompleted questionnaires. Completed patient‐reported outcomes (PRO) questionnaires will be sent to the coordinating team, with originals kept in patient records.

*Adverse event*: Will be tracked from consent to six weeks post‐rRPLND and six months post‐chemotherapy. Unresolved AEs at study end will be followed up by the Investigator but without further recording in the CRF.

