Within the good prognosis group, stage II seminoma shows the most favourable oncological outcomes with long‐term cure rates of exceeding 98%,^3^ leading to explorations of non‐SOC therapy de‐escalation to reduce treatment‐related toxicity and maintain oncological outcomes.^3^ A prospective multicentre study of a single cycle of neoadjuvant Carboplatin AUC7 with reduced field and dose of radiotherapy for stage IIA/B seminoma yielded 3‐year progression‐free survival (PFS) rate of 93.7% with minimal toxicity.^5^ In a multi‐centre cohort, three cycles of Carboplatin AUC10 monotherapy for stage II seminoma yielded a 2‐year PFS rate of 96.5% and a 3‐year cancer‐specific survival (CSS) rate of 100%^6^ with only myelosuppression being a major acute toxicity. A recent prospective clinical trial of RPLND without adjuvant chemotherapy in stage IIA/B seminoma showed a 31% recurrence rate over a mean of 26 months follow‐up.^7^ Another prospective trial of RPLND reported an 81% 2‐year recurrence free survival (RFS) and low toxicity in small volume stage IIA/B disease.^8^ Similarly, a prospective trial of nerve‐sparing RPLND for stage IIA/B seminoma showed a 10% recurrence rate at up to 9 months follow‐up.^9^ To reduce the recurrence risk, one group has adopted a single cycle of adjuvant Carboplatin AUC7 after minimally‐invasive robot‐assisted RPLND (rRPLND), which appears to have low toxicity and relapse rates.^10^

Despite high PFS rates, fewer toxicities and better quality of life outcomes, de‐escalated treatments are not yet widely adopted as SOC primarily due to a lack of comparative outcomes data derived from prospective randomised clinical trials and limited adoption of minimally invasive RPLND. Consequently, a recent UK survey highlighted significant geographical heterogeneity in SOC treatments for stage II seminoma, and only a third of centres have adopted a treatment de‐escalation regimen.^11^ TGCTs are a rare cancer and account for only approximately 1% of newly diagnosed malignant tumours,^12^ hence there are challenges in recruitment to randomised controlled trials (RCTs), including ethical concerns over randomisation without clear equipoise, and patient and clinician biases regarding SOC and de‐escalated options.

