### Secondary objectives and endpoints

3.2

1Health‐Related Quality of Life (HRQOL)
2Sexual Drive, Function and Satisfaction
3Progression‐Free Survival (PFS) and Overall Survival (OS)
PFS at 2 years is defined as the proportion of participants who do not experience disease progression or death from any cause within the 2‐year follow up period.OS at 2 years is defined as the proportion of participants who remain alive from any cause at the 2‐year follow up period.The study aims for these survival rates to remain consistent with SOC treatments (>95%).4. Safety and Treatment‐Related Complications
4Safety and Treatment‐Related Complications
The incidence, nature and severity of adverse events (AEs) will be documented according to the Common Terminology Criteria for Adverse Events (CTCAE) v5.0, from the time of informed consent until 6 weeks post‐surgery or 6 months post‐chemotherapy.Surgical complications will be classified using the Clavien‐Dindo scoring system, and additional safety assessments will include analysis of blood transfusion rates, ITU (Intensive Therapy Unit) admissions and dialysis requirements from patient records up to 6 months post‐rRPLND.

The study aims to evaluate changes in HRQOL before and after treatment(s). This will be assessed by measuring changes in domain scale scores and single‐item scores from the European Organisation for Research and Treatment of Cancer (EORTC) QLQ‐TC26 and EORTC QLQ‐C30 from baseline until the 2‐year follow up visit. 2. Sexual Drive, Function and Satisfaction

Another objective is to assess changes in sexual drive, function and overall satisfaction before and after treatment(s). This will be evaluated by tracking changes in domain scale scores and single‐item scores in the Brief Male Sexual Function Inventory (BMSFI), QLQ‐TC26 and supplementary anejaculation‐related questions, with assessments conducted from baseline to the 2‐year follow‐up visit.3. Progression‐Free Survival (PFS) and Overall Survival (OS)

The study also aims to evaluate PFS and OS rates to ensure they align with standard‐of‐care treatment outcomes.

The study seeks to assess the safety and complications associated with all treatments.

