### Adverse event reporting and harms

5.7

The Safety Reporting Instructions for the THERATEST trial outline the procedures for reporting and managing AEs and SAEs. An AE is defined as any unfavourable medical occurrence in a participant, regardless of its relationship to the research procedure. SAEs are more severe, meeting specific criteria such as being life‐threatening or requiring hospitalisation.

AEs are recorded from the time of informed consent until the safety visit and are tracked in the eCRF. Certain events, such as elective hospitalisations, are excluded from SAE reporting. SAEs must be reported to the THERATEST Coordinating Team within 24 hours using the THERATEST SAE Reporting Form. The form must be fully completed, including details like event severity, relatedness to the study and outcome. The coordinating team verifies the form's completeness and liaises with the site for any additional information. If an SAE is deemed both related to the study and unexpected, a non‐CTIMP safety report must be sent to the Research Ethics Committee (REC) within 15 days. Follow up reports are required as new information arises, ensuring thorough documentation and communication with the sponsor.

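### The rule for turning blood results into adverse events requires treatment-relatedness, which contradicts the protocol's own AE definition and is narrower than its safety endpoint

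*Protocol article*

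**What the plan says.** The blood-sample paragraph of section 5.4 opens with "Serum tumour markers (AFP, BhCG, LDH) will be taken at screening and analysed locally". It continues: "Results will be recorded in CRF, with clinically significant treatment‐related abnormalities noted as AEs".

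Section 5.7 gives the general definition: "An AE is defined as any unfavourable medical occurrence in a participant, regardless of its relationship to the research procedure". For serious events, the same section treats relatedness as something written on the form, "including details like event severity, relatedness to the study and outcome".

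The secondary safety endpoint in section 3.2 reads: "The incidence, nature and severity of adverse events (AEs) will be documented according to the Common Terminology Criteria for Adverse Events (CTCAE) v5.0". Collection starts at informed consent, and no relatedness restriction is attached.

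The blood-test panel in the first footnote of Tables 2 and 3 is wider than the one in section 5.4: "Serum tumour markers, urea and electrolytes, liver function tests and full blood count". Table 3 marks blood tests with an X in the chemotherapy column, while its footnote adds: "Test might be carried pre‐treatment for every cycle".

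**The concern.** In section 5.7 relatedness is an attribute of an event that has already been recorded. In section 5.4 it is a condition that a blood abnormality meets in order to be noted as an AE, together with a second condition, clinical significance, for which the article gives no threshold. One study would then have two routes into its AE dataset: an open one for events in general and a restricted one for laboratory findings.

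The safety results are meant to inform a definitive trial (Background). If laboratory AEs are admitted on local judgement, the reported incidence depends partly on who judged. In this study the place of treatment and the type of treatment are linked, so a difference in judgement between sites could look like a difference between treatments.

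**Working it through.** No arithmetic decides this point. The document gives no laboratory AE rate, and no rate at which abnormalities would be judged insignificant or unrelated. The check is a comparison of the stated rules.

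**1. The entry rules compared.**

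| Place | Relatedness | Significance | Start |
|---|---|---|---|
| 5.7, AE definition | not a condition | not a condition | consent |
| 3.2, safety endpoint | not a condition | severity by CTCAE v5.0 | consent |
| 5.4, blood samples | a condition | a condition, undefined in the article | not stated for this rule |

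The relatedness entry in the third row conflicts with the first row and is narrower than the second.

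**2. What the conflict removes.** Screening, where consent is taken, may fall up to 6 weeks before surgery (Table 2) or up to 2 weeks before chemotherapy (Table 3). An abnormality arising between consent and treatment cannot be related to treatment. It can be an AE under 3.2 and 5.7 but is not one under 5.4. After treatment starts, abnormalities judged unrelated go the same way. The condition can remove events and never adds one, so any bias is downward or nil.

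**3. What the rule covers.** The sentence before it names three tumour markers at screening. Read literally, the rule would have no use, because no screening result can be treatment-related. It makes sense only for blood taken once treatment has begun, which in Tables 2 and 3 includes full blood count, urea and electrolytes and liver function. That extension is an inference, and section 5.4 does not say whether those results enter the CRF.

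**4. Scheduled counts in Table 3.** With 3 cycles there are at most 3 pre-cycle samples. The first precedes any drug, which leaves 3 − 1 = 2 that can reflect earlier cycles, plus the 2-week visit. The X presents the tests as scheduled, while the footnote presents them as possible. These two statements need reconciling. The count of samples does not measure missed AEs, because AEs are collected continuously and not only on blood-test days.

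**5. Link between site and treatment.** Cohort follows whether a de-escalated treatment is institutional standard of care (5.1), three sites are planned (2.1), and all rRPLND is at a single centre (Discussion). Against that, participants who decline or are ineligible may receive BEP/EP or radiotherapy in either cohort (5.1), and rRPLND may be followed by adjuvant chemotherapy (Table 1). The confounding is partial.

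**The case against.** The strongest reply is that this is one loosely condensed phrase in an article. The full protocol and the separate Safety Reporting Instructions may hold the detailed laboratory rules, and section 5.5 describes central validation and medical coding. The sentence does not say that other abnormalities are excluded, nor who makes the judgement. A significance threshold for laboratory AEs is common practice and does not by itself contradict the AE definition. If the rule does reach full blood counts, the results are in the CRF and could be graded later. Safety is a secondary objective in a study whose primary endpoint is recruitment.

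Much of this stands. The absence of a significance threshold from an article is not a fault in itself, and no between-site difference in judgement is documented. What the reply does not remove is the relatedness condition. That is stated text, not missing detail, and it conflicts with other stated text.

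A reader might go further and infer that myelosuppression under Carboplatin AUC10 will be under-counted. The documents do not support that. The Background itself lists it as a toxicity of that regimen, "with only myelosuppression being a major acute toxicity", so it would normally pass the relatedness condition. Section 5.4 contains no test of expectedness; that appears only in 5.7, for serious events reported to the ethics committee. Only the undefined significance condition could drop a low count. Nor do the documents support saying that site and treatment effects cannot be separated at all, given the overlap described in step 5.

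**Conclusion.** The contradiction holds. Section 5.4 uses treatment-relatedness as a condition for noting a blood abnormality as an AE, while 5.7 excludes relatedness from the definition and 3.2 sets an endpoint without it. The supported consequence is a loss, in one direction only, of laboratory abnormalities judged unrelated, including any before treatment. The remainder is left to an unspecified significance judgement that may differ by site and so be partly confounded with treatment. The size is unknown and cannot be bounded from the document.

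This rests on two assumptions: that the rule is meant for blood taken after treatment starts as well as at screening, and that sites would apply it as written. If the rule covers only screening tumour markers, the relatedness condition filters no blood count, but the paragraph is then silent on recording the wider panel and still needs correcting. The change is worth making because the safety data are meant to inform a later trial. It does not affect the primary recruitment endpoint.

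**What to change.** In section 5.4, remove relatedness as a condition for entering a blood abnormality as an AE, and record attribution as a separate field, as 5.7 already does for serious events. State that the scheduled full blood count, renal and liver results falling within the AE window are entered in the eCRF and graded by CTCAE v5.0 regardless of attribution, so that the paragraph matches the panel in Tables 2 and 3. Reconcile the Table 3 footnote with the X in the chemotherapy column, without adding blood draws.

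The cost is a little extra entry of results already obtained locally, for about 30 participants. Grading every scheduled result removes the dependence on local opinion about attribution.
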